### Objectives

This study aims to conduct a high-quality randomized controlled trial to objectively evaluate the efficacy and safety of selective spinal *tuina* manipulation therapy in the treatment of childhood myopia. We hypothesize that selective spinal manipulation therapy can improve vision in children with myopia and is safer than drug therapy, with no side effects and more stable long-term efficacy.

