**Methods:**

This study is a multicenter randomized controlled clinical trial. A total of 62 children with myopia will be recruited from 4 hospitals and randomly assigned in a 1:1 ratio to a *tuina* experimental group and a drug-positive control group (tropicamide eye drops). Treatments in each group will be administered 3 times per week for a total of 8 weeks. The *tuina* experimental group will receive 20 minutes of *tuina* therapy per session, while the drug-positive control group will receive tropicamide eye drops administered every other day, with 2 drops per session. The primary outcome measures include uncorrected visual acuity and axial length, while secondary outcome measures include refractive power and accommodative amplitude. Data will be collected at baseline (week 0), on the day of completion of weeks 4 and 8 of treatment, and at the end of the 10-week follow-up period. Adverse events will be monitored and recorded throughout the study. Statisticians will be blinded. Data will be analyzed using SPSS version 28.0.

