**Conclusions:**

This study aims to evaluate the efficacy and safety of *tuina* therapy in the treatment of adolescents with myopia. We hypothesize that the therapeutic effect of *tuina* therapy is noninferior to that of tropicamide eye drops, with the additional advantages of fewer side effects and stable long-term efficacy, thereby providing reliable evidence and support for the application of *tuina* therapy in the management of myopia in adolescents.

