## Methods

### Study Design

This study is designed as a multicenter randomized controlled noninferiority trial to be conducted from June 2025 to October 2026. We plan to recruit 62 participants from 4 hospitals in Yunnan Province. Eligible participants will be randomly assigned in a 1:1 ratio to the *tuina* experimental group and the positive drug control group (tropicamide eye drops). Each participant will undergo an 8-week treatment period followed by a 2-week follow-up. Baseline information and outcomes will be assessed at baseline, at the completion of weeks 4 and 8 of treatment, and at the end of the 10-week follow-up (Figure 1). This trial adheres to the guidelines of the SPIRIT (Standard Protocol Items: Recommendations for Interventional Trials).

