### Adverse Events Reporting and Compliance Enhancement

From week 0 to week 10, detailed records of adverse events (AEs) will be documented, including type, occurrence time, severity, and duration. In the event of visual impairment, skin injuries, fainting, infections, or other serious AEs, treatment will be discontinued, and the participant will be transported to the nearest hospital. A detailed AE report will be submitted to the Ethics Committee. At the conclusion of the follow-up period, children are entitled to receive 3 sessions of pediatric *tuina* therapy at no cost; however, those who withdraw prematurely are not eligible for this benefit.

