## Discussion

### Expected Findings

This study aims to evaluate the efficacy and safety of *tuina* therapy through a randomized controlled clinical trial. We anticipate that children who receive *tuina* therapy will show improvements in AL, UCVA, SE, and AMP that are not inferior to those achieved through drug therapy. Furthermore, we expect that *tuina* therapy will be safer, free of adverse effects, and exhibit more stable long-term efficacy.

The high prevalence and severe complications of myopia have inflicted significant damage on the visual health of adolescents, imposing a substantial burden on both society and the economy. Therefore, the urgent need for an effective method to prevent and control myopia is evident. *Tuina* is a potential alternative therapy for myopia. However, current research on the application of *tuina* therapy for myopia predominantly focuses on local ocular areas, neglecting the holistic perspective, which to some extent limits its therapeutic efficacy. The holistic perspective is a fundamental concept in TCM, which views the human body as an integrated whole. This perspective posits that the human body is a harmonious entity, with the heart as the master and the 5 organs at the center, interconnected through the meridian system. This holistic entity is indivisible in terms of structural integration, functionally coordinated, and pathologically interrelated. Consequently, in the rehabilitation of myopia, it is imperative not only to address local symptoms around the eyes but also to promote the overall regulation of the child’s body.

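### Long-term efficacy is hypothesized, but observation ends 2 weeks after treatment, so the trial cannot confirm long-term stability

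*Protocol article*

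**What the plan says.** The long-term claim appears three times in the protocol article, in different strengths.

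- **Objectives:** a comparative hypothesis against drug therapy, "with no side effects and more stable long-term efficacy".
- **Discussion, Expected Findings:** an expectation that tuina will "exhibit more stable long-term efficacy".
- **Abstract, Conclusions:** a hypothesis of noninferiority to tropicamide, "with the additional advantages of fewer side effects and stable long-term efficacy". The word here is stable, not more stable.

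The observation period is set under Study Design: "Each participant will undergo an 8-week treatment period followed by a 2-week follow-up". Outcomes are assessed at baseline, "at the completion of weeks 4 and 8 of treatment, and at the end of the 10-week follow-up". The adverse events section gives the same limit: "From week 0 to week 10, detailed records of adverse events (AEs) will be documented". The section on data management counts four rounds of outcome data, the last at the end of follow-up. The article describes no later visit, extension phase or long-term endpoint.

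**The concern.** A trial can support a statement about durability only over the time for which participants are observed off treatment. Here that is 2 weeks and one visit, while the stated hypothesis concerns the long term and, in two of the three places, superiority over the drug.

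The property matters to the authors' own argument. Their Background counts rebound after stopping as a drawback of red light therapy, so persistence off treatment is part of the case for tuina as an alternative. If the hypothesis stays as worded, a result at week 10 could be taken as an answer to a question that the trial does not address.

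**Working it through.** **1. Length of observation.** Inputs from Study Design: treatment 8 weeks, follow-up 2 weeks.

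- Last assessment: 8 + 2 = week 10 from baseline. This agrees with the adverse event window, week 0 to week 10.
- Time off treatment: 10 − 8 = 2 weeks, which is 2/10 = 20% of the observation period.
- Outcome visits: weeks 0, 4, 8 and 10, four in all, as the data management section says. Only week 10 is off treatment.

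**2. Could the follow-up be longer than this?** The Abstract's Methods place the last visit "at the end of the 10-week follow-up period", and Study Design uses similar words. Read alone, that could mean 10 weeks after treatment. The 2-week follow-up in the same Study Design paragraph and the week 0 to week 10 adverse event window rule this out. The phrase means week 10 from baseline.

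**3. Could later data arise outside the described visits?** Nothing in the article points to it, and two features stand against it.

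- The Results section has enrolment continuing until October 2026 and the manuscript submitted before December 2026. A child enrolled on 1 October 2026 reaches week 10 (70 days) on 10 December 2026. The timetable leaves no room for longer follow-up.
- After follow-up, children who complete the study may receive 3 free tuina sessions, with no restriction by arm stated. Control children could then have had tuina, so a later between-arm comparison would not be clean.

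**4. What can 2 weeks show for axial length?** The documents give no elongation rate. I assume 0.2 to 0.5 mm per year, for illustration only. Growth = rate × weeks / 52.

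| Assumed rate (mm/year) | Over 2 weeks (mm) | Over 10 weeks (mm) |
|---|---|---|
| 0.2 | 0.2 × 2/52 = 0.008 | 0.2 × 10/52 = 0.04 |
| 0.5 | 0.5 × 2/52 = 0.019 | 0.5 × 10/52 = 0.10 |

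The Axial Length section accepts five readings when they differ from one another by less than 0.05 mm. The whole 2-week growth is below that limit, and a difference between arms in that growth would normally be smaller still. The mean of five readings is more precise than one reading, and the 0.05 mm limit is not a standard error, so this shows scale and proves nothing about precision. It does indicate that finding no axial length difference between weeks 8 and 10 would say little about stability.

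**The case against.** The strongest reply is that this is a matter of wording with limited consequence. The stated aims are efficacy and safety, the design is noninferiority, and long-term stability is neither a listed outcome nor part of the sample size calculation. That is correct, and it bounds the point: the primary comparison and the conduct of the trial are untouched. It does not remove the mismatch, because the claim stands in the Objectives as a hypothesis.

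The reply is also right against four stronger readings that a reader might infer.

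- *That the design can neither confirm nor refute the hypothesis.* A clear loss of effect in the tuina arm by week 10 would count against stable efficacy. What the design cannot do is confirm long-term stability.
- *That the absence of a stated week 8 to week 10 comparison is a defect.* The article sets out within-group and between-group tests and schedules both visits. A specific contrast between visits is commonly left to the statistical analysis plan, which is not at hand.
- *That persistence over 2 weeks will be reported as long-term stability.* No sentence in the article says so. It is a risk, not a stated intention.
- *That all three places claim superiority over the drug.* The Objectives and Expected Findings do. The Abstract says only "fewer side effects and stable long-term efficacy", and is comparative only in that it lists this as an additional advantage.

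**Conclusion.** The point holds in a limited form. The article hypothesizes a long-term property, and its design observes children for 2 weeks off treatment, at one visit. The trial can therefore show persistence or loss of effect up to week 10 and cannot confirm anything later. This follows from the stated schedule alone; it does not depend on sample size, power or any unseen analysis.

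It rests on one judgement: that 2 weeks is not long term. The article does not define the term. The axial length illustration rests on the assumed elongation range and is not needed for the conclusion; it bears only on which outcome could carry a claim of short-term persistence.

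The wording should be changed, because it governs what the trial may conclude. Validity of the primary comparison is not in question.

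**What to change.** 1. In the Abstract's Conclusions, the Objectives and Expected Findings, replace 'long-term' by 'up to 2 weeks after the end of treatment (week 10)', and make no claim beyond week 10. Where the text speaks of a 10-week follow-up, write 'week 10 visit' so that it is not read as 10 weeks off treatment.
2. If persistence is to be claimed, base it on the between-arm difference in change from week 8 to week 10 in logMAR uncorrected visual acuity: (week 10 − week 8 in tuina) − (week 10 − week 8 in control), with a 95% confidence interval. Higher logMAR is worse, so a claim of greater stability needs the whole interval below zero; an interval that includes zero does not show it.
3. Unless a dated analysis plan already contains this contrast, label it as a secondary analysis added after enrolment began. By December 2025, 29 of 62 children were enrolled and the article had already given an impression of results on visual acuity and axial length.
4. Report axial length change from week 8 to week 10 descriptively only, and do not read a null result as stability.

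The cost is three wording changes and at most one analysis on visits already scheduled, with no new participants or assessments. The real price is that the claim becomes less favourable to tuina.

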## Methods

### Study Design

This study is designed as a multicenter randomized controlled noninferiority trial to be conducted from June 2025 to October 2026. We plan to recruit 62 participants from 4 hospitals in Yunnan Province. Eligible participants will be randomly assigned in a 1:1 ratio to the *tuina* experimental group and the positive drug control group (tropicamide eye drops). Each participant will undergo an 8-week treatment period followed by a 2-week follow-up. Baseline information and outcomes will be assessed at baseline, at the completion of weeks 4 and 8 of treatment, and at the end of the 10-week follow-up (Figure 1). This trial adheres to the guidelines of the SPIRIT (Standard Protocol Items: Recommendations for Interventional Trials).

**Figure 1. F1:**
[figure not shown]
Flowchart of this study.

### Participants

#### Recruitment Strategy

This study will recruit 62 participants through recruitment notices in communities and hospitals from the Second Affiliated Hospital of Yunnan University of Traditional Chinese Medicine, Baoshan Hospital of Chinese Medicine, Shiping Hospital of Chinese Medicine, and Zhaotong Hospital of Chinese Medicine. Recruitment will be conducted by physicians from the *tuina* departments of hospitals. Appropriate compensation will be provided to participants upon completion of the entire procedure. Moreover, the parents or legal guardians of the participants have the right to withdraw from this study at any time and for any reason without facing discrimination or difficulties in the hospital. Participants must be children with myopia and must meet the following inclusion criteria.

#### Diagnostic Criteria

Myopia will be diagnosed according to the standards outlined in the White Paper on Myopia Control and Prevention Research established by the International Myopia Institute under the World Health Organization [28,29], as well as the “Diagnostic and Therapeutic Criteria for Internal Medicine Diseases in Traditional Chinese Medicine” (ZY/T001.1‐94), a standard of the People’s Republic of China for Traditional Chinese Medicine [30].

Mild myopia: −0.50D to −3.00DModerate myopia: −3.00D to −6.00DHigh myopia: above −6.00D

#### Inclusion Criteria

The inclusion criteria are as follows:

Children who undergo routine ophthalmic examination before enrollment and meet the diagnostic criteria for simple mild-to-moderate myopia in both TCM and Western medicineAge range: 6 to 12 years, gender-neutralGuardians and children who sign the informed consent formsGuardians and children who volunteer to participate in clinical observation, comply with the physician’s arrangements, and cooperate with treatment

#### Exclusion Criteria

The exclusion criteria are as follows:

Presence of ocular inflammation, facial dermatitis, or infectious lesionsPatients with severe systemic diseases, such as cardiovascular, cerebrovascular, hepatic, renal, hematological, and psychiatric disordersIndividuals with a history of congenital hereditary high myopiaPatients with pathological myopia fundus changes and/or significant visual impairment, or other concomitant ophthalmic diseases that may affect the assessment of efficacyChildren suffering from neurological and psychiatric disorders (eg, cerebral palsy, autism, spina bifida, anorexia nervosa)

### Sample Size

Using G*Power software to calculate the sample size, based on the preliminary pilot study results, the expected efficacy rate in the manipulation treatment group is above 80% (*P*<.05). Therefore, we set an expected effect size of 0.8. To detect between-group differences with 80% statistical power (*β*=.20), we choose a 2-tailed α level of .05. With an allocation ratio of 1:1, the required sample size was 52 participants (26 per group). Considering a 20% expected dropout rate, the final sample size was set at 62 participants (31 per group).

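### The sample size takes a between-arm effect size of 0.8 from a one-arm pilot response rate above 80%, so the stated 80% power rests on a 0.8 SD difference that nothing in the document supports

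*Protocol article*

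**What the plan says.** The Sample Size section of the protocol article names one empirical input, from a pilot study: "the expected efficacy rate in the manipulation treatment group is above 80" per cent, with a P value below .05 attached. The next sentence draws the conclusion: "Therefore, we set an expected effect size of 0.8". The scale of that effect size is not named.

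The remaining inputs are clear:
- Aim and power: "To detect between-group differences with 80% statistical power".
- Significance level: "we choose a 2-tailed α level of .05".
- Result: "With an allocation ratio of 1:1, the required sample size was 52 participants (26 per group").
- Final number: "Considering a 20% expected dropout rate, the final sample size was set at 62 participants (31 per group").

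The section gives no control-arm rate, mean difference, SD or margin. Elsewhere the article states the design as follows: "This study is designed as a multicenter randomized controlled noninferiority trial". The abstract's conclusions give the hypothesis that the "therapeutic effect of *tuina* therapy is noninferior to that of tropicamide eye drops". Under Data Analysis, between-group comparisons use the t test, or the Mann-Whitney U test if data are not normal. Under Outcomes Measures, uncorrected visual acuity (UCVA) is converted to logMAR for analysis and axial length is in mm.

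**The concern.** The word *Therefore* makes the 80% response rate the source of the 0.8. The two quantities differ in kind. The first is a proportion of responders in one arm. The second, as used, is a difference in means between two arms divided by a common SD. An 80% response with tuina is compatible with a control that does better, equally well or worse, so it fixes neither the sign nor the size of d.

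The claim of 80% power is at stake. It will shape how the result is read. If the true difference is well below 0.8 SD, a nonsignificant t test is the likely outcome. In a trial presented as noninferiority, such a result could be taken as support for the hypothesis when the trial simply had little power to see a difference.

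**Working it through.** **Inputs.** From Sample Size: effect size 0.8, two-sided alpha .05, power 80%, allocation 1:1, dropout 20%, 52 before and 62 after dropout. From Data Analysis: t test between groups. Not given: control rate, SDs, mean difference, margin.

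**1. Reproduce the stated figure.** For a two-sample t test with n per arm, the noncentrality is d × √(n/2) on 2n − 2 degrees of freedom. Power is the probability that the noncentral t exceeds the two-sided .05 critical value in absolute size.

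- n = 25, d = 0.8: noncentrality 0.8 × √12.5 = 2.828, 48 df, power 0.791.
- n = 26, d = 0.8: noncentrality 0.8 × √13 = 2.884, 50 df, power 0.807.

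The smallest n reaching 80% is 26 per arm, 52 in total, as stated. A one-sided test would need 21 per arm and does not match. So 0.8 was used as Cohen's d in a two-sided test of a difference.

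**2. Could the 80% rate yield 0.8 on another scale?** On the arcsine scale, Cohen's h = 2 arcsin √p₁ − 2 arcsin √p₂. With p₁ = 0.80, h = 0.8 requires p₂ = 0.422. With the usual two-proportion test and 26 per arm, 80% power requires a control rate of about 0.43 (0.45 with an unpooled variance). The article states no control rate, and Data Analysis plans no test of proportions. This route would need an assumption that the text does not make.

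**3. Power of 26 per arm with the planned t test.** Same formula, other true differences:

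| True difference | Power, 26 per arm |
|---|---|
| 0.8 SD | 81% |
| 0.5 SD | 42% |
| 0.3 SD | 19% |

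**4. Difference detectable with 80% power.** Solving the same formula for d:

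- 52 evaluable (26 per arm): 0.79 SD.
- 50 evaluable (25 per arm): 0.81 SD. This is what 62 children leave after 20% dropout: 62 × 0.8 = 49.6, about 50.

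**5. What this size means for noninferiority.** With truly equal arms, one-sided .025 and 80% power, the margin that can be ruled out is (1.960 + 0.842) × √(2/n) SD.

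- n = 26: 2.802 × √(2/26) = 2.802 × 0.277 = 0.78 SD.
- n = 25: 2.802 × √(2/25) = 2.802 × 0.283 = 0.79 SD.

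So the margin would have to be about 0.8 SD.

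**The case against.** The strongest defence has four parts.

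*The calculation is correct.* This stands. For d = 0.8, 26 per arm is right, and 80% power is a true statement about the t test at that difference. A reader might infer that 52 corresponds to no between-arm difference at all, or that the arithmetic is wrong. Neither follows: a true 0.8 SD difference would fit, and on rates so would a control response near 43%. The fault is in the origin of the 0.8.

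*The pilot may have held more than is shown.* The attached P value implies some test, and a condensed article may leave out means and SDs. This stands in part: that the 80% was the only source of the 0.8 cannot be proved. But the article prints a derivation, and the derivation as printed is invalid. No later document can turn a one-arm rate into a between-arm effect.

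*Noninferiority does not rule out a better result with tuina.* This stands. A reader might infer that an effect of 0.8 contradicts the hypothesis. It does not, because noninferior includes superior. The supportable statement is weaker: a large assumed difference from an active control is an odd basis for a noninferiority trial, and the article gives no reason to expect one.

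*Low powers calculated on response rates do not describe this trial.* This stands. With 80% on tuina and 26 per arm, power is 63%, 35% and 13% against control rates of 50%, 60% and 70%. It is tempting to quote these as the trial's power. They rest on assumed control rates and on a test that Data Analysis does not plan, so the powers by d are the relevant ones.

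**Conclusion.** Wrong as written. The text derives a between-arm standardised difference from a one-arm response rate, and a figure the trial relies on follows from that step. The 80% power is conditional on a true difference from tropicamide of about 0.8 SD, for which the article offers no valid support. If the truth is 0.5 SD, power is 42%, and at 0.3 SD it is 19%. These figures assume 26 evaluable per arm, equal variances, approximately normal data and two-sided .05.

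A reader might go on to infer that enrolment must rise. The document does not settle that. Without an SD, an expected difference or a margin, no single corrected sample size can be computed. What can be said is that 62 children support noninferiority with 80% power only for a margin of about 0.8 SD if the arms are truly equal.

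**What to change.** Rewrite the one paragraph under Sample Size.

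1. Delete the inference from the response rate to the effect size.
2. Name the scale of the 0.8 (Cohen's d) and give its basis. If the pilot had two arms, derive d from its between-arm means and SDs for UCVA in logMAR and axial length in mm. If it did not, say so and label 0.8 SD an assumption.
3. State what 62 children deliver: a detectable difference of 0.79 SD with 52 evaluable and 0.81 SD with 50, converted to logMAR and mm where pilot SDs allow. Give power at 0.3, 0.5 and 0.8 SD (19%, 42% and 81% with 26 per arm).
4. Say that this is power for a two-sided test of a difference, and that with truly equal arms the same numbers support noninferiority only for a margin of about 0.8 SD. The article states no margin, so there is none to align the calculation with.

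Cost: one paragraph, and a less favourable power statement. No added enrolment and no change to procedures.

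### At the stated 20% dropout, 62 enrolled children leave about 50, fewer than the 52 the plan says it requires; the allowance appears to be 52 × 1.2 instead of 52 / 0.8

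*Protocol article*

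**What the plan says.** The Sample Size section of the protocol article gives every input.

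- Error rate: "we choose a 2-tailed α level of .05".
- Power: "To detect between-group differences with 80% statistical power".
- Effect: "Therefore, we set an expected effect size of 0.8".
- Number needed before dropout: "With an allocation ratio of 1:1, the required sample size was 52 participants (26 per group").
- Number to enrol: "Considering a 20% expected dropout rate, the final sample size was set at 62 participants (31 per group").

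The formula for the dropout allowance is not printed. The Study Design section repeats the target ("We plan to recruit 62 participants from 4 hospitals in Yunnan Province"), and the Abstract and the Recruitment Strategy section give the same 62. No part of the article qualifies or corrects it.

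**The concern.** A dropout rate applies to the children enrolled. To end with a required number after a loss of 20%, that number has to be divided by 0.8. Multiplying it by 1.2 adds 20% of the smaller number, but the loss is then taken from the larger one. Since 1.2 × 0.8 = 0.96, this always leaves about 4% too few, whatever the starting figure.

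Here the requirement, the dropout rate and the enrolment target cannot all be true together. The section that justifies the trial's size therefore claims 80% power under a dropout assumption at which the trial would miss its own requirement.

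**Working it through.** **Inputs**, all from the Sample Size section: two-sided α = 0.05, power 80%, effect size 0.8, allocation 1:1, requirement 52 (26 per group), dropout 20%, final size 62 (31 per group). The article does not name the effect-size index. Reading it as Cohen's d is an assumption, used only in steps 1 and 4.

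**Step 1. Reproduce the 52.** Two-sample t test, noncentral t distribution, df = 2n − 2, noncentrality d × √(n/2).

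- n = 26 per group: 0.8 × √13 = 2.884; power 0.8075.
- n = 25 per group: 0.8 × √12.5 = 2.828; power 0.7915.

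So 26 per group is the smallest equal-group size that reaches 80%, and the stated 52 is reproduced exactly.

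**Step 2. Reproduce the 62.**

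| Rule | Total | Per group | Gives 62 (31 per group)? |
|---|---|---|---|
| N × (1 + 0.20) | 52 × 1.2 = 62.4 | 26 × 1.2 = 31.2 | yes, rounded down |
| N / (1 − 0.20) | 52 / 0.8 = 65 | 26 / 0.8 = 32.5, so 33 (66 in all) | no |

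**Step 3. Test the stated figures against each other.**

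- Children left at 20% dropout: 62 × 0.8 = 49.6 (31 × 0.8 = 24.8 per group).
- Shortfall in evaluable children: 52 − 49.6 = 2.4.
- Shortfall in enrolment: 65 − 62 = 3, or 66 − 62 = 4 with equal groups.
- Largest dropout that still leaves 52: 1 − 52/62 = 16.1%, which is 10 children.
- Check of the corrected target: 65 × 0.8 = 52.0 and 66 × 0.8 = 52.8, so both meet 52.

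This step uses only the three stated numbers and does not depend on which formula was used.

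**Step 4. Effect on power at d = 0.8.**

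| Evaluable per group | Lost of 62 | Power |
|---|---|---|
| 26 / 26 | 10 (16.1%) | 80.7% |
| 25 / 25 | 12 (19.4%) | 79.1% |
| 24.8 / 24.8 | 20% exactly | 78.8% |
| 25 / 24 | 13 (21.0%) | 78.3% |
| 24 / 24 | 14 (22.6%) | 77.4% |

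The last row lies beyond the stated 20% and shows only how power falls with further losses. With 24.8 per group, the difference detectable with 80% power is d = 0.812.

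**The case against.** Nobody disputes the arithmetic. The case on the other side is about weight and wording.

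- **The effect is slight.** Power falls by about two percentage points. Part of the margin at 52 comes from rounding to whole children, and a normal approximation would ask for only 25 per group. This stands: no conclusion of the trial is likely to turn on it.
- **The multiplication by 1.2 is inferred.** This also stands, since no formula is shown. The inference is strong, because that rule reproduces both 62 and 31 and division by 0.8 reproduces neither. The shortfall itself does not rest on it.
- **Dropouts might stay in the analysis.** The Data Analysis section lists expectation maximization, last observation carried forward or listwise deletion, and there is a week 4 assessment. Only listwise deletion clearly cuts the analysed number to about 50. Imputation does not restore the missing information, however, and a dropout allowance makes sense only if dropouts are counted as lost. The section on selection of therapists and participants also provides for withdrawing children who take up other interventions.
- **The 52 may not be secure.** The effect size of 0.8 is drawn from an expected efficacy rate, and a test for a difference is used to size a trial described as noninferiority. These are separate and larger questions. They do not repair this error, because any requirement inflated in the same way would fall short at 20% dropout.

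**Conclusion.** The concern holds. On the plan's own figures, 62 enrolled children do not leave the required 52 at 20% dropout. They leave about 50, and 62 covers at most 16.1% dropout. The shortfall is about 2 evaluable children, equivalent to 3 or 4 enrolled.

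The shortfall follows from the stated numbers alone. The loss of power, from 80.7% to about 78–79%, rests on three further conditions: 0.8 is Cohen's d, the 52 is taken as given, and dropouts contribute no data. The error is minor in size, but it is a wrong statement in the justification of the sample size and should be corrected.

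**What to change.** Keep 62 and restate the dropout sentence in the Sample Size section, for example:

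> 62 children allow for 16% dropout; at 20% dropout about 50 are evaluable and power is about 78–79% at d = 0.8 (detectable d = 0.81).

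This costs one sentence and a slightly less favourable power statement. Enrolment does not change.

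If the sponsor prefers to keep both 80% power and the 20% dropout allowance, the consistent target is 66 (33 per group), four more children. The 62 in the Abstract, Study Design and Recruitment Strategy sections would then change as well. The article reports 29 children enrolled as of December 2025 and recruitment until October 2026, so either course is still open.

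If the basis of the 52 is revised, the allowance should be recalculated from the new requirement by dividing by 0.8.
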